## Methods/Design

### Study design

This is a randomized cluster trial, stratified by regions and matched for assessment period. Pairs of eligible medical wards from different hospitals will be randomized to receive the experimental intervention (the LCP-I Program) or no intervention until the end of the trial (Figure 1). In each experimental ward, the LCP-I Program will be implemented by a Palliative Care Unit (PCU) responsible for the implementation of the Program on the ward.

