#### Sample size

An absolute increase of average scores on the Global Scale of the Toolkit of 10-15 points (in experimental wards compared to control wards) can be considered the minimum difference of clinical interest which justifies the implementation of the LCP -I Program. This increase, based on the results of the pilot study corresponds to an Effect Size (ES) of about 0.4. In order to estimate sample size in a cluster trial, along with Type I and II errors, two elements are essential: the intra-cluster correlation coefficient and the average size of the cluster (number of cluster deaths) [22]. So, for this trial:

◦ the intraclass correlation coefficient can be estimated between 0.01 and 0.05 [23]

◦ according to the review of cancer deaths on the Medical Wards potentially involved, we can expect an average number of cancer deaths in the 6 months of the assessment ranging between 15 and 20.

◦ it is foreseen that the regions participating will be able to randomize 10 pairs of Medical Wards (20 clusters overall).

Data in the Table 1 intersect three ICC scenarios (from 0.01 to 0.1) with 4 scenarios of average cluster size (from 10 to 25). In the corresponding sections the total cluster required to achieve a cluster trial with a coefficient of 80% are reported to a two-tailed alpha error of 0.5 and an a hypothetical ES of 0.4. Table 1 reports different sample size scenarios necessary to detect an ES of 0.4 with alpha = 0.05 and a power of 80% conditional to the hypothesized levels of ICC (from 0.01 to 0.10) and average size of the clusters (from 10 to 25). According to the information reported in the previous paragraphs, it seems realistic to assume that the study is feasible with a total number of clusters no greater than 20 [22].

**Table 1 T1:** Total number of clusters required according to different cluster sizes and ICC (ES = 0.4, alpha = 0.05, power = 0.80).

	Average size of the clusters			
	
Intraclass Correlation Coefficient	10	15	20	25
0.01	22	**16**	**12**	**10**
0.05	30	24	**20**	**18**
0.10	38	32	30	28

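### Table 1 makes no small-sample allowance, and the conclusion that 20 wards suffice does not hold across the plan's own planning range

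*Protocol article*

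**What the plan says.** All of the following is in the protocol article, Statistical methods, Sample size, unless noted.

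- The planning inputs are an effect size of about 0.4, an ICC between 0.01 and 0.05, an average of 15 to 20 cancer deaths per ward in the six-month assessment, and 10 pairs of wards (20 clusters).
- The text states that "Table 1 reports different sample size scenarios necessary to detect an ES of 0.4 with alpha = 0.05 and a power of 80" per cent.
- Table 1 is captioned "Total number of clusters required according to different cluster sizes and ICC (ES = 0.4, alpha = 0.05, power = 0.80". It crosses ICC 0.01, 0.05 and 0.10 with cluster sizes 10, 15, 20 and 25. The four cells at the corners of the planning range are 16 and 12 wards (ICC 0.01, with 15 and 20 deaths) and 24 and 20 wards (ICC 0.05, with 15 and 20 deaths). Cells of 20 or fewer are in bold, apparently to mark what is feasible.
- The conclusion drawn from these inputs is that "it seems realistic to assume that the study is feasible with a total number of clusters no greater than 20".
- One sentence gives the significance level as a "two-tailed alpha error of 0.5 and an a hypothetical ES of 0.4". The next sentence, the caption of Table 1 and the Statistical analysis section give 0.05.
- Under Study design: "This is a randomized cluster trial, stratified by regions and matched for assessment period". Under Statistical analysis, the primary model is a hierarchical linear model adjusted for the average baseline level of quality of care. The sample size section takes no explicit credit for matching or for baseline adjustment.

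**The concern.** There are two separate points.

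First, wards are the randomised units, so the precision of the treatment contrast is estimated from the variation between wards. With 20 wards and no other terms that estimate has about 18 degrees of freedom, and with 10 wards only 8. A calculation with normal quantiles treats the variance as known, and at 10 to 30 clusters this understates the number of wards needed.

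Second, the table and the text disagree. One cell inside the planning range requires more wards than the text says are needed.

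At stake is the reading of a null result. If the ICC is near 0.05, the trial has less power for an effect of 0.4 SD than the stated 80%, and a reader of the protocol would not know it.

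**Working it through.** **Inputs (Sample size section and Table 1).** ES = 0.4; two-sided alpha = 0.05; power = 0.80; m deaths per ward; ICC as listed; K wards in total, split 1:1. As in the plan, m counts deaths.

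**Step 1: reproduce Table 1.** Patients per arm without clustering: 2 × ((1.960 + 0.842)/0.4)² = 98.1. Multiply by the design effect DE = 1 + (m − 1) × ICC, divide by m, round up per arm, and double.

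- ICC 0.05, m = 20: DE = 1.95; 98.1 × 1.95/20 = 9.57 per arm, rounded up to 10; K = 20. Stated: 20.
- ICC 0.05, m = 15: DE = 1.70; 98.1 × 1.70/15 = 11.12 per arm, rounded up to 12; K = 24. Stated: 24.

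All 12 cells come out exactly: 22/16/12/10, 30/24/20/18 and 38/32/30/28. Table 1 is therefore a normal-quantile calculation for an unmatched, unadjusted comparison. It reproduces with alpha 0.05, so the 0.5 is a misprint.

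**Step 2: replace normal by t quantiles.** Noncentrality = 0.4/√(4 × DE/(K × m)), and power comes from the noncentral t distribution on K − 2 degrees of freedom.

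Example, K = 20, m = 20, ICC 0.05: 0.4/√(4 × 1.95/400) = 2.864. Against 1.960 the normal calculation gives 81.7%. Against the t critical value on 18 degrees of freedom, 2.101, the noncentral t gives 77.3%. With 22 wards it is above 80%.

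For all cells, wards stated, power of that number with t, and wards needed with t:

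| ICC | m = 10 | m = 15 | m = 20 | m = 25 |
|---|---|---|---|---|
| 0.01 | 22: 77.1%, 24 | 16: 77.0%, 18 | 12: 72.6%, 14 | 10: 70.2%, 12 |
| 0.05 | 30: 79.3%, 32 | 24: 79.4%, 26 | 20: 77.3%, 22 | 18: 76.6%, 20 |
| 0.10 | 38: 78.6%, 40 | 32: 78.1%, 34 | 30: 79.3%, 32 | 28: 78.9%, 30 |

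Every cell is below 80%, and every cell needs exactly 2 more wards.

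**Step 3: power of the 20 wards foreseen, over the planning range.**

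| ICC | Deaths per ward | Wards in Table 1 | Normal | t, 18 df | Wards needed (t) |
|---|---|---|---|---|---|
| 0.01 | 15 | 16 | 90.1% | 86.6% | 18 |
| 0.01 | 20 | 12 | 95.6% | 93.4% | 14 |
| 0.05 | 15 | 24 | 75.7% | 71.0% | 26 |
| 0.05 | 20 | 20 | 81.7% | 77.3% | 22 |

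At the middle of the range (ICC 0.03, 17.5 deaths) 20 wards give 86.4% by the normal calculation and 82.5% with t.

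By the plan's own method one corner of four fails at 20 wards. With t on 18 degrees of freedom both ICC 0.05 corners fail.

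**The case against.** **The text is a hedged feasibility judgement, and the 24 is printed openly.** Three of the four corner cells need 20 wards or fewer, and the 24 is left out of bold. A reader might infer that the 20-ward conclusion fails altogether on the plan's inputs. The documents do not support that: 20 wards are enough at ICC 0.01 and at mid-range, even with t. What stands against the plan is that the sentence draws on the stated range without saying that part of it is not covered.

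**Normal quantiles are a common approximation, not an arithmetic slip.** That is right, and in several cells the shortfall is under one point. At the planned size with ICC 0.05, though, it is 4 to 5 points, and it moves the 20-death cell from 20 to 22 wards.

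**The planned analysis adjusts for baseline quality.** This could recover power. As an assumption of mine, with t on 17 degrees of freedom at ICC 0.05: removing 20% of the between-ward variance gives about 81% at 20 deaths per ward, while at 15 deaths about 50% must be removed to reach 81%. The article gives no figure for the gain, so the objection shows what could be claimed, not what has been shown.

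**Pair matching.** Because wards are randomised in pairs, a reader might infer that only 9 degrees of freedom are available and that power is lower still. The Statistical analysis section describes no pair effect, and such a figure would charge the full cost of matching while crediting none of its variance gain. It is not used here.

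**Type I error.** A reader might also infer that the false-positive rate will exceed 5%. That would follow only if the analysis used normal-based inference. The article does not say so, and the degrees-of-freedom method may properly sit in an analysis plan that is not shown.

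**Conclusion.** The point holds in two limited parts.

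1. Table 1 overstates power. With ward-level degrees of freedom and no adjustment, its cells deliver 70% to 79% rather than 80%, and each is 2 wards short.
2. The limit of 20 wards does not hold across the planning range. At ICC 0.05, 20 wards give 76% (15 deaths) and 82% (20 deaths) by the plan's own method, and 71% and 77% with t on 18 degrees of freedom. At ICC 0.01 it holds comfortably.

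The second part needs no new method for the 15-death corner, because Table 1 itself prints 24. The t figures assume equal cluster sizes, an effect of 0.4 SD, K − 2 degrees of freedom, and no gain from baseline adjustment or matching. The alpha of 0.5 is an evident misprint with no effect on the table.

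**What to change.** - Recompute Table 1 with t quantiles on ward-level degrees of freedom: 24/18/14/12 for ICC 0.01, 32/26/22/20 for ICC 0.05 and 40/34/32/30 for ICC 0.10.
- Next to it, state the power of 20 wards at the four corners of the planning range: 87%, 93%, 71% and 77%, in the order of the Step 3 table.
- Qualify the feasibility sentence so that it says 20 wards do not reach 80% power at the ICC 0.05 end.
- If credit is wanted for baseline adjustment or matching, state the assumed variance reduction and show the resulting power, with the degrees of freedom that the analysis will use.
- Correct alpha from 0.5 to 0.05.

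The cost is one recomputed table and two or three sentences. The design and the number of wards need not change. At 20 wards and ICC 0.05, the power that can be claimed falls by 4 to 5 points against the normal-quantile figures.

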### Statistical analysis

The centers and patients characteristics will be reported as mean and standard deviation (SD) or frequency and percentage, respectively, for continuous and categorical variables. The distribution of variables of clusters allocated as experimental or control wards will be compared with the t-Student test or one way ANOVA (for ordinal or continuous variables) and with the Pearson Chi-square (for binary or nominal variables).

The assessment of the primary end-point will take into account the clustered design of the trial through the use of hierarchical linear models [24,25]. These models will be adjusted for the average level of quality of care provided to the baseline assessment. The results will be expressed in terms of beta coefficients of regression or in estimated marginal means, 95% Confidence Intervals (IC 95% CI) and level of significance. P-value < 0.05 will be considered statistically significant. The same approach will be used for the assessment of the continuous secondary end-points where there are continual variables. For the assessment of categorical secondary end-points with categorical variables, the hierarchical logistical model will be used.

All the analysis will be conducted using the SAS Statistical Package Release 9.1 (SAS Institute, Cary, NC, USA).

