**Figure 2 F2:**
[figure not shown]
**Design of the assesment procedures**.

Immediately after randomization the PCU responsible for LCP-I implementation on the experimental ward will complete, as quickly as possible, all the organizational procedures required for the implementation of the Program. At the same time the Regional Coordination Structure will start baseline assessment in the experimental and control wards.

Baseline assessment will be performed by evaluating the quality of end-of-life care in each pair of randomized wards for all eligible cancer deaths in the 3 months before the randomization date (months -1 to -3 in Figure 2).

The LCP-I Program will be implemented in the experimental ward by the PCU (t1 to t6, Figure 2). The LCP-I Program has a duration of 6 months from the beginning of the intensive training (months 1-6 in the figure). No intervention will be implemented in the control ward until the end of the evaluation.

Effectiveness assessment (t7 to t12, Figure 2) will be performed by evaluating the quality of end-of-life care in each pair of randomized wards for all eligible cancer deaths occurring in the six months after the conclusion of the LCP-I Program in the experimental ward (months 7 to 12 in Figure 2).

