### Procedures of assessment (Figure 3)

**Figure 3 F3:**
[figure not shown]
**Procedures of assesment for the eligible population**.

Primary and secondary end-points will be evaluated for all eligible cancer deaths as follows:

**1. Identification of eligible cancer deaths from the ward: **the cancer deaths in the ward will be identified through the hospital's deaths documentation (which lists all deaths regardless of cause). Cancer deaths will be identified by the International Classification of Diseases-Ninth Revision (ICD-IX) criteria, applied to the causes of death as reported in the death certificate of the Italian National Institute of Statistics (ISTAT).

**2. Access to medical and nursing documentation **for the assessment of care procedure

3. Assessment of care procedures

**4. GP identification: **name, address and telephone number of the GPs will be obtained by medical documentation. However, all information are available in the Regional Health records.

**5. Caregiver identification: **information regarding the patients' principal caregiver (name, relationship, address and telephone number), as reported in the medical documentation, must be acquired. The principal caregiver is the person who was closest to the patient during his/her last week of life in hospital. It can be a family member (most frequent) or a friend. If the patient had no caregiver, the interview cannot be performed and the circumstances should be described in detail.

**6. Letter to GPs: **an official letter, signed by the Regional Coordinator, describing the survey and announcing the telephone interview is sent to the deceased' GPs.

**7. GPs telephone Interview: **this must take place within 4 months of the patients death and focuses on two aspects:

◦ communication between ward staff and GPs

◦ confirmation or integration of information regarding the patient's caregiver (name, relationship, address and telephone number).

**8. Final Caregiver identification: **obtained from two main sources: medical documentation and/or patients' GPs.

**9. Caregiver Letter: **an official letter, signed by the Regional Coordinator, introducing the study and announcing the telephone interview is sent to the caregiver.

**10. Phone contact with caregiver: **it occurs 4-5 days after the letter is sent out. The interviewer refers to the contents of the letter and invites the caregiver to participate in an interview at a location of their choice.

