1. collection and elaboration of data in the patients' medical documentation

2. contact and interview with the caregivers

Regarding collection and elaboration of data from patients' medical documentation:

• the processing of data included in medical documentation is considered of significant public interest, to that purpose, in agreement with Articles 20 and 21 of the Italian Confidentiality Laws, it is accessible to the National Health Service and other Public Health organizations for the planning, management, monitoring and evaluation of healthcare;

• in theory the evaluation could be subject to informed consent of the terminal cancer patients (patients who might die of cancer). In fact, the patients involved in the Program evaluation, who are nearly always incapable of giving valid consent, are identified after death (as cancer deaths), regardless of whether they were hospitalized in a ward where it LCP-I Program was implemented;

• in all cases, where the patients are competent and aware of their health status (parameters previously assessed independently in the LCP-I Program) and where there is considered no risk to the patient, the clinical ward staff will be trained to deliver information to the patient and to ask them the consent to the use of personal data. This procedure will be recorded in the medical records;

• during the study and in subsequent publications, any personal data will be disaggregated and made anonymous.

Regarding contact with the caregivers, the initial contact will be made through a personal letter which includes detailed information and requests their permission to be contacted by telephone. The caregiver will be contacted by phone after at least 3 days and will be invited to participate in the interview. The interview will be conducted by specifically trained staff.

This procedure has been used successfully in the ISDOC survey [21], with very satisfactory results:

• sampling of 2,000 cancer deaths in 30 Italian Local Healthcare Authorities' areas.

• caregiver identification in 95% of cases (N = 1900)

• realization of 1271 valid interviews (64% of the sample).

• reasons for non-completion of the interviews: no caregiver identified (5%), refusal (20%), caregiver not contactable (8%), other (3%).

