This study can be interpreted as a Phase III trial according to the MRC framework. In this study, the effectiveness of a fully defined intervention is assessed by comparing the distribution of the endpoints in the experimental arm and in the control arm. Although not all dying patients will be supported by the LCP Program, the assessment is planned on the whole sample of patients deceased in the experimental ward and in the correspondent control ward.

Cluster trial are often used for assessing interventions directed at a hospital team [22]. The validity of this protocol is supported by the results of a recent Cochrane Review [38] on the effectiveness of end-of-life pathways. The review did not find any randomised controlled trials, quasi-randomised trial or high quality controlled before and after studies, to include in the analysis. The authors concluded that there is a lack of evidence supporting such practice [38], and recommend the use of cluster randomised trials as the most effective study design in evaluating this approach [38].

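### The primary model names one covariate, a noisy ward baseline mean taken from other patients; a few patient covariates should be named in advance as well

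*Protocol article*

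**What the plan says.** The Statistical analysis section says that the primary analysis will "take into account the clustered design of the trial through the use of hierarchical linear models", and then: "These models will be adjusted for the average level of quality of care provided to the baseline assessment". No other covariate is named. The same section describes the sample, "The centers and patients characteristics will be reported as mean and standard deviation (SD) or frequency and percentage", and compares the arms with t-tests or ANOVA and chi-square tests. It does not say what follows from those comparisons.

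Under General procedures of the cluster trial, the baseline set is the cancer deaths in the 3 months before randomisation. The effectiveness set is "all eligible cancer deaths occurring in the six months after the conclusion of the LCP-I Program in the experimental ward". These are different people. Under Ethical issues, patients are "identified after death (as cancer deaths), regardless of whether they were hospitalized in a ward where it LCP-I Program was implemented", so the list of deaths is complete in both arms.

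The primary score, however, comes from a caregiver interview that can be declined. The precedent survey cited under Ethical issues reports "realization of 1271 valid interviews (64% of the sample"), with 20% refusal and 8% not contactable.

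**The concern.** In a cluster trial whose patients arise after allocation, the covariates should describe the patients who are actually rated. Here the named covariate describes an earlier group, averaged to ward level. If the arms differ in the age, sex or cancer site of the patients whose caregivers agree to be interviewed, the stated model does not adjust for it.

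There is one arm-specific route by which response could differ. Families in experimental wards receive two leaflets, one of them at a meeting after the death, and the interview follows at 2 to 4 months. The documents do not say that this changes participation.

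Between-arm significance tests with no stated consequence also leave open a decision on adjustment after the results are seen. At stake are a little precision and protection against the measurable part of a shift in who is rated.

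**Working it through.** **Inputs.** From Sample size: ES 0.4, two-sided alpha 0.05 (as in the Table 1 title), power 80%, ICC 0.01 to 0.05, 15 to 20 deaths per ward in 6 months, 20 wards (10 per arm). From Ethical issues: 64% interview yield. The R² values, covariate effects and response patterns below are assumptions.

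**1. The plan's own figure.** n per arm = 2 × ((1.960 + 0.842)/0.4)² = 98.1. Multiply by 1 + (m − 1) × ICC, divide by m, round up and double. At ICC 0.05 and m = 20: 98.1 × 1.95/20 = 9.6, so 10 per arm and 20 in total. All 12 cells of Table 1 reproduce.

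**2. How good the named covariate is.** Three months at the planned rate give 7.5 to 10 deaths per ward. At 64% this is 4.8 to 6.4 interviews. Reliability of the ward mean = ICC/(ICC + (1 − ICC)/n):
- ICC 0.05: 0.05/(0.05 + 0.95/4.8) = 0.20, and 0.05/(0.05 + 0.95/6.4) = 0.25.
- ICC 0.01: 0.05 to 0.06.

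**3. Chance imbalance.** With 20 × 0.64 = 12.8 interviews per ward there are 128 per arm. For a characteristic with 50% prevalence, the SE of the arm difference is √(2 × 0.25 × (1 + 11.8 × ICC)/128). This is 6.9 points at ICC 0.02 and 9.2 points at ICC 0.10 (these ICCs are for the characteristic). If the characteristic shifts the score by 0.2 to 0.5 SD, one such SE moves the estimate by 0.2 × 0.069 = 0.014 to 0.5 × 0.092 = 0.046 SD. The SE of the effect itself is √(2 × 0.1242/10) = 0.158 SD (step 5), and it already includes this variation.

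**4. Response that differs by arm.** Take a binary factor with 50% prevalence that shifts the score by 0.5 SD, and 64% response in both groups of the control arm.

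| Experimental response (factor absent/present) | Bias, ward mean only | Bias, factor added |
|---|---|---|
| 64%/64% | 0.00 SD | 0.00 SD |
| 54%/74% | 0.039 SD | 0.001 SD |
| 49%/79% | 0.062 SD | 0.003 SD |

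These come from 2,000 simulated trials (20 wards, ICC 0.05, 20 effectiveness and 10 baseline deaths per ward). By hand, the second row is 0.5 × (0.74/1.28 − 0.50) = 0.039. Over factor effects of 0.2 to 0.5 SD and prevalence differences of 5 to 20 points, bias is 0.01 to 0.10 SD, or 2.5 to 25% of ES 0.4.

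If response follows satisfaction itself, with the more satisfied half of experimental families responding a = 5 to 15 points more often, bias = 0.798a/(1.28 + a) = 0.03 to 0.08 SD. Patient covariates remove only the part of this that they predict.

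**5. Precision.** The variance of a ward mean is ICC + (1 − ICC)(1 − R²)/m, with R² the share of within-ward variance explained. At ICC 0.05 and m = 12.8:

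| R² | Variance | Reduction | Power (noncentral t, 18 df) |
|---|---|---|---|
| 0 | 0.1242 | – | 67.0% |
| 5% | 0.1205 | 3.0% | 68.3% |
| 10% | 0.1168 | 6.0% | 69.7% |

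At 15 deaths per ward (15 × 0.64 = 9.6 interviews), power goes from 59% to 61–62%. At ICC 0.01 and m = 12.8 it goes from 82% to 83–85%. No credit is taken here for the baseline adjustment.

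**The case against.** The strongest reply is that this is an article, not the full analysis plan. Its sentence names one covariate without excluding others, and adjusting for the baseline outcome is a valid choice. That stands as far as it goes: nobody can say from the article that further covariates are ruled out. But the article chose to state the adjustment, and what it states is a single ward-level term, so improving it is a fair proposal.

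The design safeguards are also real. Patients are a complete count from death certificates in both arms, and the same procedure applies throughout. Selection acts only through caregivers.

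Three stronger readings are tempting, and the documents support none of them.
- **That chance imbalance distorts the estimate.** It does not; the confidence interval covers it.
- **That response is known to differ by arm.** No passage shows this, and the 64% comes from a survey, not from this trial.
- **That the Discussion claims full coverage when it says "the assessment is planned on the whole sample of patients deceased in the experimental ward and in the correspondent control ward".** The whole sentence means that patients are assessed whether or not they were supported by the pathway. The article is open about missing interviews: Procedures of assessment covers patients without a caregiver, and Ethical issues prints the 64%.

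A power of 72% can be reached only by also assuming that the covariates explain 20% of between-ward variance, for which the documents give no basis.

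**Conclusion.** The point holds in a limited form. The one covariate named is a weak measure of ward level (reliability 0.20 to 0.25 at ICC 0.05, about 0.05 at ICC 0.01) and describes other patients. Measured differences between arms in the mix of rated patients are therefore not adjusted for in the model as stated.

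A reader might infer that the primary estimate is biased by case mix. That is not established: with equal response in both arms the bias is nil. If response does differ by arm along a measured factor, the assumed scenarios give 0.01 to 0.10 SD, at most a quarter of ES 0.4.

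The gain in power is 1 to 3 points under an assumed within-ward R² of 5 to 10%. Satisfaction-driven non-response would mostly remain. This is an inexpensive improvement, not a flaw that threatens the trial.

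**What to change.** In Statistical analysis, state that the primary hierarchical model also includes patient age, sex and cancer site (grouped in a few categories), taken from the death certificate or chart, as pre-specified individual-level fixed effects beside the ward baseline mean. Say that adjustment does not depend on the between-arm significance tests.

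The cost is a few patient-level parameters, which use no ward-level degrees of freedom, and some programming. One point must be confirmed first. The article gives no list of abstracted patient variables; the caregiver details are specified ("name, relationship, address and telephone number), as reported in the medical documentation, must be acquired"), but age and sex are not named. Availability for all eligible deaths is therefore an inference, though a reasonable one given access to certificates and charts.

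A sensitivity analysis that weights interviewed patients by the inverse of their estimated response probability, by arm, is optional. The Discussion wording needs no change.
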